## Abstract

Age-related lens opacification (cataract) remains the leading cause of visual impairment and blindness worldwide. In low- and middle-income countries, utilization of cataract surgical services is often limited despite community-based outreach programmes. Community-led research, whereby researchers and community members collaboratively co-design intervention is an approach that ensures the interventions are locally relevant and that their implementation is feasible and socially accepted in the targeted contexts. Community-led interventions have the potential to increase cataract surgery uptake if done appropriately.

In this study, once the intervention is co-designed it will be implemented through a cluster-randomized controlled trial (cRCT) with ward as a unit of randomization.

This study will utilise both the qualitative methods for co-designing the intervention and the quantitative methods for effective assessment of the developed community-led intervention through a cRCT in 80 rural wards of Dodoma region, Tanzania (40 Intervention). The ‘intervention package’ will be developed through participatory community meetings and ongoing evaluation and modification of the intervention based on its impact on service utilization. Leask’s four stages of intervention co-creation will guide the development within Rifkin’s CHOICE framework. The primary outcomes are two: the number of patients attending eye disease screening camps, and the number of patients accepting cataract surgery. NVivo version 12 will be used for qualitative data analysis and Stata version 12 for quantitative data. Independent and paired t-tests will be performed to make comparisons between and within groups. P-values less than 0.05 will be considered statistically significant.

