### Sample size, randomization, and allocation concealment

Using the sample size calculation method for unmatched cRCTs described by Hayes and Bennett [34], it is calculated that 40 wards will need to be enrolled in each study arm to achieve 80% power to detect a minimum 30% increase in screening examination and cataract surgery acceptance rates associated with the intervention at the 95% confidence level.

Population data from the 2022 Tanzanian national census (accounting for predicted population growth up to 2023) will be used, we expect an average of 1420 adults aged over 50 years in each study ward (coefficient of variation = 0.43).

The sample size calculation method for unmatched cluster-randomized trials with rate outcomes described by Hayes and Bennett was used:
c=1+Zα/2+Zβ2λ0+λ1y+k2λ02+λ12/λ0-λ12where c is the number of clusters, $Z_{\alpha /2}$ is the standard normal distribution based on level of significance (1.96), $Z_{\beta }$ is the standard normal distribution value based on the power of $100\left(1-\beta \right)\%$ (using 80% power $Z_{\beta }=0.84)$, $\lambda_{0\;}$ and $\lambda_{1}$ rates of the outcome in absence and presence of intervention, respectively, y is the person-years of follow-up in each group ward, and k = 0.4 is the coefficient of variation of the population rates between wards within each group. To detect a minimum 30% difference in outcome rates comparing intervention to control wards, we calculate that we will need to enrol 39 wards in each study arm for the presentation at screening camps outcome (outcome 1), and 42 wards in each arm for the cataract surgery outcome (outcome 2). To sufficiently power the study for both outcomes, we will sample a total of 40 wards in each study arm taking into account the design effect as well.

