## Description of variables

### Outcomes variables

#### Primary outcome

The primary outcome will be the proportion of all eligible persons with operable cataract who accepted and show up for cataract surgery at the base hospital overall and stratified by age, sex, and VA levels. Based on the 2022 population census, the appropriate population of people aged 50 years and above will be sought from the ward authorities for denominator calculation.

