#### Secondary outcomes

Proportion of all eligible persons attending at outreach eye examinations sites overall and stratified by age, sex, and VA levels (Screening rates)Acceptability, appropriateness, and fidelity of the community-led intervention. At study outset, distance of each study ward from the base hospital will be measured. Social economic status of each ward, Education levels, and economic activities of each ward will be obtained from the recent released National censors results.
*Acceptability* of the intervention will be assessed by using the standardized Acceptability of Intervention Measure questionnaires to evaluate the affective attitude, burden, perceived effectiveness, and ethicality of an intervention [35, 36].
*Appropriateness* will be assessed by using the Intervention Appropriateness Measure questionnaires to measure the perceived need, suitability, alignment, or compatibility of the intervention with the context, culture, or priorities of the participants and the research team [36].
*Fidelity* which is the extent to which the intervention is delivered or implemented as intended by community will be assessed using the Fidelity of Implementation Rating System checklist that evaluates the adherence, quality, and differentiation of an intervention delivery [37, 38].

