## Statistical analysis and data management

Analysis for baseline characteristics will be through descriptive statistics and level of significance at 0.05% will be considered significance. Results will be analysed by Intention-to-treat analysis in which clusters are analysed as to their group which were randomized prior will be used to determine the mean differences between arms using t-tests or Wilcoxon test (as appropriate) and mixed effects regression modelling of cataract surgery acceptance rate will be done so as to account for clustering at the ward level. Results will be reported as the difference in primary and secondary outcome between the intervention and control arms. We will conduct sensitivity analyses controlling for any imbalances in remaining baseline characteristic at participant and cluster level. Because mixed effects models are robust to data missing at random (MAR), we will assess data missingness. If missing data are not MAR, we will conduct multilevel multiple imputation.

Further quantitative descriptive analyses will be used to provide an understanding of the trial results that require further explanation (e.g. control clusters that demonstrate substantial improvement in outcomes, despite not receiving intervention, and reason for not attending surgery).

The trial will be reported using the 2012 CONSORT guidelines, with the updated cRCT extension [39].

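### The abstract names two primary outcomes and the Methods one, so the error rate and power depend on the section followed; the 0.05% level is a separate slip

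*Protocol article*

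**What the plan says.** **Status of the outcomes.** The Abstract says "The primary outcomes are two: the number of patients attending eye disease screening camps, and the number of patients accepting cataract surgery". The Primary outcome section names one: "The primary outcome will be the proportion of all eligible persons with operable cataract who accepted and show up for cataract surgery". Screening attendance, worded as "Proportion of all eligible persons attending at outreach eye examinations sites", appears under Secondary outcomes.

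Other sections lean both ways. Sample size labels screening as outcome 1 and surgery as outcome 2, gives 39 and 42 wards per arm for them, and settles on 40 per arm with the aim of powering both. Study design and target population treats both kinds of uptake as the main focus of this component. Monitoring speaks of the primary outcome in the singular.

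**Measure.** The abstract counts patients. Study population and follow-up uses rates per person-year (0.198 for screening, 0.045 for surgery, in controls). The Primary outcome section uses a proportion of persons with operable cataract, then says that the ward population aged 50 and over will be obtained for the denominator.

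**Level.** The abstract says "P-values less than 0.05 will be considered statistically significant". Sample size uses a normal deviate of 1.96 and a 95% confidence level. Statistical analysis and data management says "level of significance at 0.05% will be considered significance".

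**The concern.** Which outcome is primary decides which result makes the trial positive, and the protocol fixes this in two incompatible ways. The split result is plausible here. Table 1 shows that the package adds community sensitization and, separately, support to reach the base hospital, so attendance could rise while surgery does not. Participants and data collectors are not masked, so a choice left open until results are known invites selective reporting.

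The false-positive rate and the power also differ between the readings, so the 80% power at the 95% confidence level quoted in the sample size section does not describe all of them. The shift in measure adds to this: even with surgery agreed as primary, the reader cannot tell which surgery statistic is meant.

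**Working it through.** **Inputs (Study population and follow-up; Sample size).** Control rates λ0 = 0.198 (screening) and 0.045 (surgery) per person-year; 30% increase, so λ1 = 0.2574 and 0.0585; k = 0.4; z = 1.96 and 0.84; 40 wards per arm. Person-years per ward, y, are 2840 (1420 adults over two years). The text attaches 2840 to an arm, but the formula needs a ward figure, so y = 1420 is shown as well.

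**Step 1: reproduce the stated ward numbers.**

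c = 1 + (1.96 + 0.84)² × V, with V = [(λ0 + λ1)/y + k²(λ0² + λ1²)]/(λ0 − λ1)².

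- Screening, y = 2840: V = (0.000160 + 0.016873)/0.003528 = 4.828; c = 1 + 7.84 × 4.828 = 38.9.
- Surgery, y = 2840: V = (0.0000364 + 0.0008716)/0.00018225 = 4.982; c = 1 + 7.84 × 4.982 = 40.1.
- With y = 1420: 39.2 and 41.6, which round to the stated 39 and 42.

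The plan's figures therefore rest on a full two-sided 5% for each outcome, with no split between them.

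**Step 2: power at 40 wards per arm.** Power = Φ(√(39/V) − 1.96).

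- Screening: √(39/4.828) = 2.842, so Φ(0.882) = 0.811 (0.808 at y = 1420).
- Surgery: √(39/4.982) = 2.798, so Φ(0.838) = 0.799 (0.783 at y = 1420).

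**Step 3: what each reading implies.** The documents give no correlation between the two test statistics, so a range is assumed, using a bivariate normal. Joint power is at y = 2840.

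| Correlation | Either wins at 0.05: family-wise error | Both must win: power |
|---|---|---|
| 0 | 1 − 0.95² = 9.75% | 0.811 × 0.799 = 65% |
| 0.5 | 9.1% | 69% |
| 0.8 | 7.8% | 74% |

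As correlation approaches 1, the error falls towards 5% and joint power rises towards the smaller single power, about 80%. Surgery as sole primary: error 5%, power 78–80%.

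**Step 4: if either may win, with 0.025 each.** The same formula needs 47 (screening) and 49 (surgery) wards per arm at y = 2840, or 48 and 51 at y = 1420. With 40 wards, power is about 0.73 and 0.71, or 0.72 and 0.69.

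All these powers are for rates per person-year. They do not carry over to a proportion among persons with operable cataract, for which the protocol gives no sizing inputs of its own.

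**The case against.** The Methods can be read coherently. The outcome sections define one primary outcome, Monitoring uses the singular, and the mixed-effects model is specified for surgery acceptance only. Sizing for screening as well is compatible with a powered secondary outcome, and the labels 1 and 2 confer no primary status. On that reading only the abstract is out of line. This argument supports surgery as the natural choice, but it does not remove the conflict: the abstract's statement is explicit and nothing in the document overrides it.

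Three stronger readings are tempting and are not supported.

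- *That the protocol adopts a rule under which either outcome wins at 0.05.* No section states a success rule, and the abstract's P-value sentence is general; it does not say that each primary is tested separately. The error and power figures show what follows from possible rules. A testing order or alpha split could sit in an analysis plan that is not shown, so its absence is not the point made here.
- *That 0.05% is a real threshold, leaving power near 25%.* The sentence opens with baseline characteristics, and a level of 0.0005 would need 92 to 98 wards per arm by the plan's own formula, against the stated 39 and 42. The abstract's 0.05 and the 1.96 and 95% in the sample size section all point to 5%.
- *That 0.05% is the only level in the Methods.* The sample size section, also in the Methods, gives 1.96 and 95% confidence.

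Independence is also an unlikely extreme. Camp attendees with operable cataract are counselled and referred for surgery, so positive correlation is plausible. That is why the range runs to 0.8.

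**Conclusion.** The contradiction over the primary outcome stands. It concerns what the document states, so an unseen analysis plan does not excuse it. Its size depends on the reading: family-wise error of about 7.8% to 9.75% if either may win, joint power of about 65% to 74% if both must, and 5% error with about 78–80% power for surgery alone. These figures assume the plan's own rates, a 30% increase, k = 0.4, 40 wards per arm and correlations from 0 to 0.8. The shift between count, rate and proportion is part of the same defect. The 0.05% is a separate wording error with no likely effect on how the trial would be analysed.

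**What to change.** State one primary set, with one outcome measure and one denominator, in the Abstract, Sample size, Primary outcome and Secondary outcomes sections, and bring the wording in Study design and target population into line.

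The simplest choice, following the Methods, is cataract surgery as sole primary outcome at two-sided 5%, with screening as secondary. Screening could, for example, be tested at 5% only if surgery is significant; that is one acceptable option among several. No wards are needed beyond the 40 per arm planned if the 78–80% power is accepted and the primary measure remains the rate that was sized. If the proportion is kept, the power should be restated for it. The downside is small: a screening effect is not confirmatory if surgery fails.

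If both stay primary, say whether either (with an alpha adjustment) or both must succeed, and restate the power accordingly.

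Correct 0.05% in the analysis section to 5% (0.05). The cost is mainly wording, but a change to the primary set of a protocol that already has ethical clearance should be recorded as such, before outcome data are seen.

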## Introduction

The recent released WHO data have shown there are at least 2.2 billion people worldwide who are visually impaired. In at least 1 billion cases, the problem could have been prevented or has yet to be addressed, particularly cataract [1, 2].

In all world regions, women bear most of the blindness and vision impairment at 55%. This is largely due to social factors where women do not get to access surgical services with the same frequency as men [1–3]. Several studies have shown that the cataract surgical coverage among women in Sub-Saharan Africa (SSA) and South Asia is nearly always lower, sometimes only half that in men [4–6].

The barriers to utilizing cataract surgical services in SSA are well known: lack of treatment awareness, fear of surgery, poor geographical access, and inability to pay for direct and indirect costs [5, 7–9]. However, there is still limited evidence about what works to mitigate these barriers and factors associated with low utilization.

There is some observational evidence that bringing eye health services closer to community, coupled with other health system interventions, have led to an increase in the volume of cataract surgeries in countries and districts targeted by Vision 2020: right to sight programme [10, 11]. Most of this evidence comes from studies that applied before-after designs thus posing several limitations in generating rigorous evidence and generalization of findings [6, 12–14].

Recent randomized control trials and systematic reviews, while finding little evidence for non-community-led interventions to improve access to cataract surgery, did find evidence that community-led interventions have the strongest chance of improving health seeking behaviour at the community level [12, 13, 15]. In a community-led intervention, a community identifies its own needs and mobilizes itself to respond to those needs [16, 17].

In this study, the process for the development of the community-led intervention will be based on the recently suggested circle by Leask *et al*. in which they described four stages: Planning (framing the aim of the intervention), Conducting (Defining the intervention and co-creation), Evaluating (the process and the effectiveness through the cluster-randomized controlled trial (cRCT) in this case), and Scaling (of the findings and possibility of scaling up the intervention) [18]. The aim is to produce community-led health interventions that are more effective, efficient, and sustainable than those of traditional investigator-led trials [15, 19, 20]. This model has proven to be effective in controlling Dengue virus transmission in Mexico and improving nutrition status in several Tanzanian communities and has been advised by various studies as best means to address some of the complex public health issues by tailoring interventions [21–24]. However, this study will be the first of its kind in the field of eye health services research aiming at co-developing, implementing, and evaluating the impact of a ‘community-led intervention package’ for increasing cataract surgery uptake in rural Tanzania among adults of 50 years and above.

The Leask *et al*. four stages will be guided by Rifkin’s CHOICE Framework. This framework is a tool to evaluate and plan community-led health interventions that aim to promote equity and empowerment. The framework is based on the work of Amartya Sen, a Nobel laureate economist and philosopher [25, 26]. The framework uses the acronym CHOICE to describe six criteria that distinguish between target-oriented and empowerment approaches to participation. The criteria are: **C**ontrol over resources—while carrying out this trial decisions on how to allocate and use resources for the intervention should be discussed by the community and agreement reached. **H**ealth improvement—explaining to the community the expected health outcomes of the intervention and how are they will be measured. **O**rganizational characteristics—how is the community need to be organized for the intervention will be discussed. **I**nstitutionalization—how will the intervention be integrated into the existing health system and sustained over time, need to be discussed at every stage. **C**apacity building—skills and knowledge of the community members and community health workers enhanced by the intervention implementation. **E**nabling environment—Leadership, communication, and ethical issues need to be addressed during the co-created intervention.

The primary objectives are (i) to co-design a community-led intervention for increasing the uptake of eye health services, including presentation at screening camps and accepting cataract surgery and (ii) to implement the community-led intervention through a cRCT and assess its effectiveness and explore how implementation-related factors influence the achievement of the desired outcomes in different sociocultural settings of Dodoma region, Tanzania.

## Methods and analysis

### Study area

The study will be conducted in Dodoma region of Tanzania. Dodoma is administratively divided into eight district councils. Currently, there are a total of 3.08 million people, 209 wards and people aged 50 years and above account for approximately 10% of the population [27]. Dodoma is one of the regions with the highest prevalence of cataract blindness at 17.7%, which is above the national average of 15% [28]. To address eye health care needs, the regional eye care team has established a regular eye outreach programme since 2017. This justify and favours the settings of this trial to be done in Dodoma region, as there is ongoing community eye outreach programmes (CEOP) aiming at screening patients at their communities. These were initiated by the regional health committee and they have not shown to be very promising in increasing cataract services uptake and henceforth this community-led trial is designed. The current CEOP is done twice each month by a team of assistant ophthalmic medical officers, optometrist, ophthalmic nursing officer, and a Programme coordinator. The main activities entail screening for refractive errors and simple eye diseases by use of a pen torch. Those needing further management and/or surgery are listed down and referred to a base hospital.

### Overall study design

This protocol paper is structured conforming to the Standard Protocol Items: Recommendations for Intervention Trials (SPIRIT) 2013 Checklist [29]. The project will be having two components as (i) Intervention co-creation component using participatory action research approaches [i.e. Focus Group Discussions (FGDs), and Key Informant Interviews (KIIs)] (ii) Assessment of effectiveness and scaling of the intervention through a cRCT. A community-led participatory action research design was chosen because the intervention development and implementation will largely be locally designed and adapted by communities. A community-led participatory action research study design offers an ideal opportunity to engage the community at every stage to develop their own intervention package and implemented for assessment of effectiveness of the interventions, the role of implementation factors, and strategies facilitating the sustainability and scaling up of the intervention package. The cRCT was chosen because it avoids the selection biases and provides a robust way of getting strong correlation of study variables. In this setting, a cluster is defined as an administrative ward which usually has a typical population ranging from 8000 to 12,000.

### Study component I: Community-led intervention co-creation

#### Study design and co-creation process

This component involves a qualitative participatory approach, mainly for the intervention co-development process using the four stages (Planning, Conducting, Evaluating, and Scaling) of participatory action research methods.

**Planning Stage:**
Objective: This stage will entail framing of the aim of the study together with the district and ward leaders so as to get the participants for next stage.Participants: Leaders of Selected pilot 3–4 wards including local health facility in-charge, District eye care coordinators and other first-hand informants of eye health in the ward. As a first step, the research team will meet leaders of selected wards to explain the community-led intervention design process (CLIDP). They will be asked for their assistance in identifying key stakeholders for involvement in the CLIDP through the open community meeting as outlined in Fig. 1Sampling: Leaders of the respective wards will be requested to identify stakeholders for the community-led intervention design process.Methods: Qualitative techniques entailing secondary data review to obtain the contact of the ward leaders so as to engage onto this stage together with community open meetings to identify stakeholders for next stage.
**Conducting stage**
Objectives: The research team will be interested in finding out the perceived levels of cataract visual impairment needing surgery, and the factors that act as facilitators or barriers for accepting cataract surgery.Participants: Identified stakeholders of the concerned wards will be engaged in this stage.Sampling: Representatives of the identified community groups within each ward which include beneficiaries of eye health services, women’s group representatives, youth and religious leaders, community leaders/elders, and health facility in chargeMethods: This will entail open community meetings, FGDs, and KIIs of the above groups. The Study team will be led by social scientist who will be providing the technical aspect of data collection in this stage together with the study coordinator and an ophthalmologist. Community representative upskilling will be done prior to the engagement; it entails training on the purpose, process, and expectations of co-creation of the intervention through the use of FGD and KII. This will include explanation of role of the facilitator, the importance of active listening, the types of questions and responses, aim of co-creation and the ethical principles of confidentiality and respect. Further community upskilling will be provided as need arise. For feasibility reasons, the intervention development component will involve a small sub-sample of 3–4 intervention wards (purposefully sampled), and a total of 12–15 FGDs and 6–8 KII are planned to be conducted. The development of interview questions will be guided by findings from a recent RAAB Study in nearby regions of Tanzania [4, 30–32].
